### Criteria for discontinuing or modifying allocated interventions {11b}

If the intubator cannot intubate at the given tube mark, he will be allowed to change the site of grip—the site change will be noted from the video. If he/she still fails, the consultant can take over.

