#### Dropout criteria

Any change in grip after holding the ETT, giving backward-upward-right-posterior pressure (BURP) to the larynx after holding ETT, or manipulation of the ETT like changing the curvature of the tube or rotating it by 180° will be video recorded but will be excluded from the final analysis. If any video has a conflict of opinion between the assessors regarding time to intubation or method of intubation, it will be excluded from the final analysis.

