#### Technique

After induction and a minimum of 3 min of administering the paralytic agent, the intubator will perform the laryngoscopy. Once the intubator declares that the CL grade is optimal (CL < 3), it will be confirmed by the faculty or senior either verbally or visually. Once declared as an “optimum laryngoscopic view,” the tube will be handed over by the technician to the intubator and prior instruction will be given to take the first attempt at the marked point, with the elbow close to the body, with the thumb at the plastic marker, index, and middle fingers opposite [2]. If the above will be difficult, then any change in methodology will be allowed as per the faculty’s decision and will be documented from the video. The whole procedure will be videographed.

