### Outcomes {12}

Primary outcome measures: time to intubation (TTI) in both groups. The TTI will be calculated from holding the ET to removing the laryngoscope—after declaring a tube passed “under vision.” The frame has been chosen to reduce bias due to laryngoscopy problems or delay due to attaching the circuits and ventilating till capnographic confirmation of correct tube position. The primary outcome will be described in seconds.

Secondary outcome measures assessed will be first-pass intubation success rate; intubation difficulty scores (IDS) [6]; ease of the intubation assessed by the intubator, faculty, and a blinded assessor unrelated to the study on the Likert scale (0—very easy to 5—extremely difficult); and incidence of complications (bleeding or sore throat) in each group. The IDS comprises of attempt (in no), additional operators (if any, then in no), alternative technique: stylet/bougie, Cormack Lehane grading (CL grade: I/II/III/IV), lifting force: normal (0)/increased (1), external laryngeal pressure required during insertion of the tube: no (0)/yes (1), and position of vocal cords: abducted (0)/adducted (1).

Assessments from the video footage: These assessments will be done by two different anesthesiologists independently. The mean values will be used for analysis after disputes/disagreements (if any) are settled by a third person not belonging to the research team. This will reduce bias due to possible errors in time calculations.

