**Assessments**					
Demographic characteristics	**X**				
Airway assessment	**X**	X			
Experience of the intubator (in months)		X			
Time of holding of ET (T1)			**X**		
Time of removal of laryngoscope (T2)				**X**	
Time to intubation (from T1 to T2)			**X**	**X**	
Intubation difficulty score			**X**		
Any change in the site of holding the tube			**X**		
Videography during intubation		**X**	**X**	**X**	
Ease of intubation on Likert scale by the intubator			**X**	**X**	
Ease of intubation assessed by faculty			**X**	**X**	
Ease of intubation assessed by a blinded assessor					**X**
Incidence of airway trauma (bleeding/sore throat )			**X**		**X**

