### Methods in analysis to handle protocol non-adherence and any statistical methods to handle missing data {20c}

Sensitivity analysis will be done to handle the missing data. Missing data will be handled with multiple imputations. Per-protocol and ITT analyses will both be done.

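### Grip changes are allowed, excluded from the final analysis and promised to the ITT set, with no scoring rule, so a rescue at another site can be credited to the allocated site

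*Protocol article*

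**What the plan says.** Three groups of statements in the protocol article bear on a trainee who does not succeed with the hand at the mark.

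- **The change is allowed.** Under Technique, "prior instruction will be given to take the first attempt at the marked point"; if that proves difficult, "any change in methodology will be allowed as per the faculty’s decision and will be documented from the video". Section {11b} adds: "If the intubator cannot intubate at the given tube mark, he will be allowed to change the site of grip". The site change is noted from the video, and then: "If he/she still fails, the consultant can take over".
- **The case is removed.** The Dropout criteria begin with "Any change in grip after holding the ETT" and exclude such videos from the final analysis. Eligibility criteria {10} also exclude procedures in which the trainee departs from the methodology or the consultant takes over.
- **The case is kept.** Section {20a} describes an analysis of all randomised patients, and section {20c} says: "Per-protocol and ITT analyses will both be done".

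On endpoints, section {12} says: "Secondary outcome measures assessed will be first-pass intubation success rate". It then lists the IDS items, the first of which is the number of attempts. It does not say what ends a pass or an attempt. The Participant timeline {13} schedules "Any change in the site of holding the tube" as an assessment at intubation, but neither the Secondary objectives nor section {12} lists it as an outcome, and it is not an IDS item.

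**The concern.** The stated aim is to find out whether the holding site affects intubation once a good view has been obtained. Abandoning the allocated site because the tube would not pass there is direct evidence on that question. The plan records the event from the video but gives it no agreed place in the results.

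Two things can happen to it. In the ITT set, a tube that would not pass at one site and passed after the hand moved can be scored as a first-pass success, with a single IDS attempt, for the site that failed. In the set that applies the dropout rule, the patient disappears. Either way, first-pass success and IDS can look more alike between the arms than the sites really are. Because the scoring is open, the same video can also be entered as a first-pass failure with two attempts.

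**Working it through.** The document gives no figure for first-pass success or for how often the grip is changed, so there is no stated number to reproduce. The check is a reading of the text followed by an illustration.

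**Step 1: follow one patient through the text.** The tube does not pass at the mark, the trainee moves the grip, and the tube passes.

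| Question | Source | Answer |
|---|---|---|
| Was the change allowed? | Technique; {11b} | Yes |
| Is the patient in the final analysis? | Dropout criteria; {10} | No |
| Is the patient in the ITT analysis? | {20a}; {20c} | Yes |
| Is it a first-pass success? | {12} | Not stated |
| Is it one IDS attempt or two? | {12} | Not stated |

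**Step 2: the two available scorings in the ITT set.** Section {11b} runs from the mark, to a new grip, to the consultant, and mentions neither withdrawal of the laryngoscope nor a new attempt. The Dropout criteria list a grip change beside laryngeal pressure applied after the tube is held and rotation of the tube, which are manoeuvres possible within one laryngoscopy. That supports scoring one attempt and a success. The Technique section ties the first attempt to the marked point, which supports scoring a second attempt and a failure. The text does not choose.

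**Step 3: illustration with assumed rates.** Let p be the first-pass success rate with the grip at the mark, and r the share of at-mark failures rescued by a grip change, taken as equal in both arms.

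- Rescues credited to the allocated site: p + r(1 − p)
- Rescued cases dropped: p / [1 − r(1 − p)]

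Assume p = 80% and 90%, a true difference of 10.0 points, with the planned 180 per arm. At r = 50%:

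- Credited: 0.80 + 0.5 × 0.20 = 90% and 0.90 + 0.5 × 0.10 = 95%, a difference of 5.0 points.
- Dropped: 0.80/0.90 = 88.9% and 0.90/0.95 = 94.7%, a difference of 5.8 points.

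| r | Difference, credited | Power, credited (180 per arm, two-sided 5%) | Difference, dropped |
|---|---|---|---|
| 0% | 10.0 | 76% | 10.0 |
| 25% | 7.5 | 62% | 8.1 |
| 50% | 5.0 | 44% | 5.8 |
| 75% | 2.5 | 24% | 3.2 |

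The dropped column keeps unrescued failures in the denominator. Section {10} also excludes consultant take-overs, so that set could lose still more failures.

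**Step 4: an extreme case, also assumed.** Suppose 95% of tubes pass at first laryngoscopy in both arms, after a change of grip in 10% of one arm and 2% of the other, and every change succeeds.

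- Credited: 95% v 95%, a difference of 0.
- Dropped: 85/90 = 94.4% v 93/98 = 94.9%, a difference of about 0.5 points.
- Success at the allocated site: 95 − 10 = 85% v 95 − 2 = 93%, a difference of 8 points.

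These inputs were chosen to show how far the masking can go. They are not a forecast.

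**The case against.** The strongest reply is that the document never says a grip change falls within the same attempt or counts as a first-pass success. A reader might infer both from {11b}, but the instruction to make the first attempt at the mark supports the opposite: a re-grip would be a second attempt, hence a first-pass failure. That stands, so the point is that crediting is permitted, not that it is planned.

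Second, the Dropout criteria already deal with these patients. That is true of the set that applies them, but the same article promises an ITT analysis of all randomised patients, and dropping the cases also hides the event.

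Third, the event is not wholly lost to the outcomes. Time to intubation runs from holding the tube to removing the laryngoscope, so if the blade stays in, time spent failing and re-gripping is charged to the allocated arm. The ease ratings may reflect it too. This stands and limits the concern mainly to first-pass success and IDS.

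Fourth, attributing results to the assigned arm is what ITT does, and a definition of first pass may be left to a fuller document. Both are fair in general. Here, however, the article itself states the permission, the exclusion and the ITT promise, and these conflict. An ITT comparison with re-gripping credited also answers a question about starting at a site with re-gripping allowed, which is not the stated aim.

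A reader might also infer that masking a difference favours the trial, because the Trial design calls it an equivalence trial. The document does not support that. The sample size is computed for two-sided equality, no equivalence margin is stated for these outcomes, and the background expects holding farther from the tip to be better.

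**Conclusion.** The concern holds in limited form. The sections that allow a grip change, exclude it and promise ITT cannot all be applied to the same patient as written, and no rule fixes how the change is scored. A rescue at another site can therefore be credited to the site that failed or removed from view, and either can shrink a true difference in first-pass success and IDS.

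The size cannot be taken from the document. In the Step 3 illustration a 10-point difference falls to between 7.5 and 2.5 points if rescues are credited, and to between 8.1 and 3.2 points if they are dropped, for r from 25% to 75%. This rests on the assumed success rates and on an equal rescue share in both arms. If a re-grip is scored as a second attempt in the ITT set, first-pass success there is not diluted.

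The outcomes affected are secondary, and the primary outcome may still capture part of the delay. The change is worth making, but the point does not undermine the trial.

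**What to change.** - **Reconcile the analysis sets.** State that the exclusions in Eligibility criteria {10} and the Dropout criteria do not remove grip-change cases from the ITT set promised in {20a} and {20c}.
- **Define the endpoint in {12}.** First-pass success is placement by the trainee in one laryngoscopy with the grip at the mark. Any change of site is scored as failure at the allocated site, in both arms.
- **State the IDS rule.** Say how a change of site counts in the attempt item.
- **Report the event.** List change of site by arm as a secondary outcome, and keep success with any grip as a supportive figure.

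The care rule in {11b} is unchanged. Recruitment is under way and an interim analysis is planned after 120 cases, so the wording should be dated and, if possible, settled before the arms are compared.

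The cost is wording only, since the change of site is already to be read from the video. There are two downsides. The reported success rate will be slightly lower. The endpoint will also depend partly on a decision to switch made by a trainee or faculty member who is not blinded. Showing the switch rate by arm and the any-grip figure lets readers judge how much that matters.

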### Strategies to improve adherence to interventions {11c}

All residents and faculty will be informed about the study protocol for improving adherence. The intubator will be instructed about the procedure, and a transparent film shall be marked on the tube to guide the intubator on the site of holding.

### Relevant concomitant care permitted or prohibited during the trial {11d}

For the study, no standard treatment shall be withheld. No differential treatment or partiality in any form will be extended to a patient who has refused to be a part of the study or who voluntarily withdraws from the study at any point.

### Provisions for post-trial care {30}

In the unlikely event of any untoward events arising from the intervention, the researchers will treat them within the available institutional facilities’ bounds.

The center where the study is done is a 900-bedded institute. It is well equipped with adequate resources and facilities to cater to any possible untoward events arising because of the intervention.

### Outcomes {12}

Primary outcome measures: time to intubation (TTI) in both groups. The TTI will be calculated from holding the ET to removing the laryngoscope—after declaring a tube passed “under vision.” The frame has been chosen to reduce bias due to laryngoscopy problems or delay due to attaching the circuits and ventilating till capnographic confirmation of correct tube position. The primary outcome will be described in seconds.

Secondary outcome measures assessed will be first-pass intubation success rate; intubation difficulty scores (IDS) [6]; ease of the intubation assessed by the intubator, faculty, and a blinded assessor unrelated to the study on the Likert scale (0—very easy to 5—extremely difficult); and incidence of complications (bleeding or sore throat) in each group. The IDS comprises of attempt (in no), additional operators (if any, then in no), alternative technique: stylet/bougie, Cormack Lehane grading (CL grade: I/II/III/IV), lifting force: normal (0)/increased (1), external laryngeal pressure required during insertion of the tube: no (0)/yes (1), and position of vocal cords: abducted (0)/adducted (1).

Assessments from the video footage: These assessments will be done by two different anesthesiologists independently. The mean values will be used for analysis after disputes/disagreements (if any) are settled by a third person not belonging to the research team. This will reduce bias due to possible errors in time calculations.

### Participant timeline {13}

**Table Taba:** 

	Study period				
	Enrolment allocation	Post-allocation			
Timelines	Before surgery	Before intubation (induction to mask ventilation)	Intubation	Post-intubation	Post-extubation
**Enrollment**					
Informed consent	X				
Eligibility criteria	X				
Allocation	X				
**Interventions**					
Group 1 (19 cm)					
Group 2 (24 cm)					
**Assessments**					
Demographic characteristics	**X**				
Airway assessment	**X**	X			
Experience of the intubator (in months)		X			
Time of holding of ET (T1)			**X**		
Time of removal of laryngoscope (T2)				**X**	
Time to intubation (from T1 to T2)			**X**	**X**	
Intubation difficulty score			**X**		
Any change in the site of holding the tube			**X**		
Videography during intubation		**X**	**X**	**X**	
Ease of intubation on Likert scale by the intubator			**X**	**X**	
Ease of intubation assessed by faculty			**X**	**X**	
Ease of intubation assessed by a blinded assessor					**X**
Incidence of airway trauma (bleeding/sore throat )			**X**		**X**

### Sample size {14}

Based on the pilot study, the mean time to intubation was found to be 8.83 s, a standard deviation of 4.07 s, and a variance of 16.57 s. Using this information—an allocation ratio of 1:1, to ascertain a 20% difference in time to intubation between the two groups, it was calculated that a sample size of at least 149 participants in each group is necessary to detect a difference of 1 s in time to intubation in between the groups, if we allow a significance level of 5% and power our study at 85%. Thus, a total sample size to demonstrate the minimum effect size is 298, and assuming approximately 20% loss and rounding up to the nearest number, the total sample size required is 360 (180 in each group). The calculation was done using online sample size calculators http://powerandsamplesize.com and http://www.sample-size.netusing comparison of means for two-sided equality and the normal approximation using the *Z* statistics instead of the *T* statistics. The calculated sample size was concordant between the two calculators used.

We felt a 20% difference in time to intubate (TTI) as defined by us in the study would be clinically significant, as this difference means greater manipulations after the tube is inside the oral cavity resulting in more significant trauma and complications of intubation.

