**Sample size:**

To detect a 20% difference in time to intubation between groups with a significance level of 5% and power of 85%, we will need a total of 298 patients. Accounting for data loss, we plan to recruit 180 patients in each group.

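### The sample size of 149 per group fits neither stated target: power is 56% for 1 s and 96% for a 20% difference, not 85%

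*Protocol article*

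**What the plan says.** Sample size {14} takes its planning values from a pilot study: "the mean time to intubation was found to be 8.83 s, a standard deviation of 4.07 s, and a variance of 16.57 s". The method is "comparison of means for two-sided equality and the normal approximation", with Z rather than t statistics, 1:1 allocation, a 5% significance level and 85% power. One sentence gives two targets. It first sets out to find a 20% difference in time to intubation, then concludes that "a sample size of at least 149 participants in each group is necessary to detect a difference of 1 s in time to intubation". The section continues: "Thus, a total sample size to demonstrate the minimum effect size is 298". The recruitment target follows: "assuming approximately 20% loss and rounding up to the nearest number, the total sample size required is 360", that is 180 per group.

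The Abstract mentions only the relative target. It opens with "To detect a 20% difference in time to intubation between groups with a significance level of 5% and power of 85" per cent and gives a total of 298. The last paragraph of Sample size {14} explains why 20% matters clinically. No reason is given anywhere for 1 s.

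**The concern.** On a mean of 8.83 s, 1 s and 20% are different targets, so one sample size cannot give 85% power for both. The figure of 298 is also what the two-sample formula returns per group for 1 s, which suggests that a per-group result was taken as the total and halved.

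Three things depend on this:

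- **Reading a null result.** If the trial is believed to have 85% power for 1 s, a non-significant result will be taken as good evidence against a difference of that size. The true chance of missing it is about 44%, not 15%. Trial design {8} calls the trial an equivalence trial, which makes this misreading more likely.
- **The interim analysis.** The section on retention and follow-up {18b} describes an interim look that may lead to stopping or to a change in sample size, and Interim analyses {21b} places it after 120 cases. Such a decision needs one correct target difference.
- **The loss allowance.** The eligibility and dropout criteria remove cases from the analysis after randomization, so the allowance will be used.

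**Working it through.** **Inputs, all from Sample size {14}:** mean 8.83 s; SD 4.07 s (4.07² = 16.56, in line with the stated variance of 16.57); two-sided 5%, z = 1.960; 85% power, z = 1.036; sum of the two z values 2.996; 1:1 allocation.

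**1. Reproducing the plan's figure.** For two means under the Z approximation, n per group = 2 × (2.996 × SD / δ)².

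- δ = 1 s: 2 × (2.996 × 4.07 / 1)² = 297.5, so **298 per group**, 596 in total.
- Without the factor 2 (a one-sample form): 148.7, so 149.

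The stated 149 therefore appears only when the factor 2 is lost, or equivalently when 298 per group is read as the total. Other two-sample forms do not give 149: one-sided for 1 s, 239; one-sided for 20%, 77; an effect of 0.2 × SD, 449; equivalence with a 1 s margin, 316 to 383.

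**2. The two targets.** 0.20 × 8.83 = 1.766 s, and 1 / 8.83 = 11.3%.

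- δ = 1.766 s: 2 × (2.996 × 4.07 / 1.766)² = 95.4, so **96 per group**, 192 in total.

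**3. Power at the planned sizes.** SE = 4.07 × √(2/n), power = Φ(δ/SE − 1.960), and the difference detectable with 85% power = 2.996 × SE.

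| n per group | SE (s) | Power, 1 s | Power, 1.766 s | Detectable at 85% |
|---|---|---|---|---|
| 149 | 0.4715 | Φ(0.161) = 56.4% | 96.3% | 1.41 s (16.0%) |
| 180 | 0.4290 | 64.5% | 98.4% | 1.29 s (14.6%) |

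Using t instead of Z makes almost no difference: 56.1% and 96.2% at 149 per group.

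**4. Loss allowance.** 298 × 1.2 = 357.6, which rounds up to 360. Allowing for 20% loss means dividing: 298 / 0.8 = 372.5, so 373. Conversely, 360 × 0.8 = 288, which is 10 short of 298, and 1 − 298/360 = 17.2%. With 144 per group left, power for 1.766 s is 95.7%.

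**The case against.** The strongest reply is that 20% is the target the authors defend. The Abstract names only that one, and the clinical argument in Sample size {14} is made only for it. For 20% the trial has more patients than it needs, so the 56% is a real shortfall only if 1 s was meant. This is correct, and it is why no more patients are asked for. It does not rescue the printed statement, which ties 149 per group and 85% power explicitly to 1 s and is wrong for 20% as well, in the other direction.

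The calculator output is not shown, so the per-group/total mix-up is an inference. The exact match at 298 makes it the evident cause, and the discrepancy stands whatever the cause. The loss point is small, since the plan says only approximately 20%; it belongs in the same correction but carries little weight alone.

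A further caution is that every power figure rests on SD 4.07 s. The only pilot described, in the explanation for the site of holding the tube, used 54 experienced anesthesiologists, whereas the trial uses trainees. The article does not say outright that the timing figures come from that pilot. With 144 per group, power for 1.766 s stays at 85% or more up to an SD of 1.766 / (2.996 × √(2/144)) = 5.0 s. That caveat is fair, but it applies equally to the plan's own calculation.

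**Conclusion.** The concern holds. From the plan's own inputs, 1 s needs 298 per group and 20% (1.77 s) needs 96 per group, so 149 per group matches neither at 85% power. No other section reconciles the figures. The stated power is too high by about 29 percentage points for 1 s (85 − 56) and too low by about 11 for 20% (96 − 85). Even if all 360 patients were analysed, power for 1 s would be about 64%. For the one difference the protocol justifies, the planned size is ample. The error is in what the protocol claims, not in the number of patients. These conclusions assume the stated SD of 4.07 s, equal groups and the two-sided Z comparison of means that the plan specifies.

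**What to change.** Keep recruitment at 360 and correct both the Abstract and Sample size {14}:

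- Name 20%, 1.77 s on a mean of 8.83 s, as the target difference, and delete the statement about 1 s.
- State that 96 per group (192 in total) gives 85% power for 1.77 s, and that 149 evaluable per group gives about 96% power for 1.77 s, or 85% power for 1.41 s (16%), all with SD 4.07 s.
- State that 360 allows for about 17% loss if 298 are to remain, and that a 20% loss leaves 144 per group with about 96% power for 1.77 s.

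The cost is wording only, with no extra patients. What is given up is the claim to 85% power for 1 s. If the authors did intend 1 s, that claim could be kept only with 596 evaluable patients, or 746 recruited (2 × 373) at 20% loss.
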